## Abstract

**Background:**

Hypothyroidism is a prevalent endocrine condition. Individuals with this disease are commonly managed through supplementation with synthetic thyroid hormone, with the aim of alleviating symptoms and restoring normal thyroid stimulating hormone levels. Generally this management strategy is effective and well tolerated. However, there is research to suggest that a significant proportion of hypothyroid sufferers are being inadequately managed. Furthermore, hypothyroid patients are more likely to have a decreased sense of well-being and more commonly experience constitutional and neuropsychiatric complaints, even with pharmacological intervention.

The current management of hypothyroidism follows a biomedical model. Little consideration has been given to a biopsychosocial approach to this condition. Within the chiropractic profession there is growing support for the use of a biopsychosocial-based intervention called Neuro-Emotional Technique (NET) for this population.

**Methods/Design:**

A placebo-controlled, single-blinded, randomised clinical pilot-trial has been designed to assess the influence of Neuro-Emotional Technique on a population with primary overt hypothyroidism. A sample of 102 adults (≥18 years) who meet the inclusion criteria will be randomised to either a treatment group or a placebo group. Each group will receive ten treatments (NET or placebo) over a six week period, and will be monitored for six months. The primary outcome will involve the measurement of depression using the Depression, Anxiety and Stress Scale (DASS). The secondary outcome measures to be used are; serum thyroid stimulating hormone, serum free-thyroxine, serum free-triiodothyronine, serum thyroid peroxidase auto-antibodies, serum thyroglobulin auto-antibodies as well as the measurement of functional health and well-being using the Short-Form-36 Version 2. The emotional states of anxiety and stress will be measured using the DASS. Self-measurement of basal heart rate and basal temperature will also be included among the secondary outcome measures. The primary and secondary measures will be obtained at commencement, six weeks and six months. Measures of basal heart rate and basal temperature will be obtained daily for the six month trial period, with recording to commence one week prior to the intervention.

**Discussion:**

The study will provide information on the influence of NET when added to existing management regimens in individuals with primary overt hypothyroidism.

**Trial Registration:**

ANZCTR Number: 12607000040460

## Background

Hypothyroidism is a frequently encountered clinical condition and is the most common cause of pathological hormone deficiency. Hypothyroidism is classified as either congenital or acquired, based on the time of onset. The condition is further categorised based on level of endocrine dysfunction and severity. Primary hypothyroidism follows a dysfunction of the thyroid gland itself, whereas secondary hypothyroidism results from failure in the machinery or mechanisms peripheral to the thyroid gland (eg. hypopituitarism). Overt hypothyroidism defines the clinical manifestation of the condition, and the term mild hypothyroidism is assigned to the subclinical variants of the disease [1]. The diagnosis of hypothyroidism is based on a thorough history, clinical findings and laboratory analysis. Although a deficit in thyroid hormones and their resultant action has a varying systemic influence, individuals with overt hypothyroidism frequently present with fatigue, depression, cold intolerance, weight gain, hoarseness, dry skin, bradycardia, constipation and slowed mental processing [2]. Laboratory testing in individuals with primary overt hypothyroidism typically depicts an elevated serum thyroid stimulating hormone (TSH) level, and a decrease in serum free-thyroxine (FT4) levels [3]. One of the major causes of acquired hypothyroidism is chronic autoimmune thyroiditis (Hashimoto's Disease) in which laboratory testing may reveal auto-antibodies to the thyroglobulin protein (Anti-Tg), and the thyroid peroxidase enzyme (Anti-TPO) [4,5].

The gold standard treatment for individuals with hypothyroidism is supplementation using a synthetic version (Levothyroxine Sodium) of the thyroid hormone - thyroxine [1]. Patients are typically given a supplemental dose (1.8 μg/kg in adults) of levothyroxine sodium daily for an indefinite period of time, with the aim of improving the function of the patient and restoring appropriate TSH levels [1]. Once an appropriate dose has been established, thyroid hormones levels are monitored every 6-12 months to ensure the adequacy of treatment [6]. Treatment dose may be altered based on a number of different variables; treatment efficacy; comorbid-illness; significant alterations to weight; oestrogen use; pregnancy; age [1,7].

The treatment of individuals with hypothyroidism typically follows a biomedical paradigm. There are clearly defined biochemical boundaries for what constitutes the clinical manifestation of hypothyroidism and standard algorithms to guide the commencement and progression of treatment. Several studies however have reported inadequate treatment (as determined by thyroid blood markers) in a significant proportion (20%) of individuals with 'managed' hypothyroidism [8,9]. Saravanan *et al *report that substantial numbers of hypothyroid sufferers continue to experience the plethora of hypothyroid symptoms despite demonstrating hormone levels within reference ranges [10].

Whybrow *et al *state that almost 100% of severe hypothyroid sufferers are found to have significant concurrent depression [11]. Grozinsky-Glasberg *et al *state that hypothyroid patients are more likely to have a decreased sense of well-being and more commonly experience constitutional and neuropsychiatric complaints as compared to euthyroid individuals [12]. Practitioners must take care when initiating treatment for hypothyroidism in certain populations (ischemic heart disease, adrenal cortical insufficiency) and be mindful of avoiding adverse drug interactions [1].

After an exhaustive search of the medical literature it would appear that little consideration has been given to the concept of a biopsychosocial-based management approach to this condition. Within the chiropractic profession there are anecdotal reports and case studies [13] to suggest that a biopsychosocial-based treatment approach may be applicable to hypothyroidism. This manuscript has been compiled to outline the methodology for a randomised-controlled clinical study investigating a biopsychosocial approach to primary overt hypothyroidism that adheres to the CONSORT [14] checklist in its design.

## Methods

The objectives of this research are described below:

1) To determine whether the addition of NET to concurrent management regimens can improve clinical outcomes in a sample of individuals with primary overt hypothyroidism. For Example, reducing the severity of depression scores at six weeks and six months; 2) To determine the short and medium term responses to NET via changes to the primary and secondary outcomes in this sample.

### Design

An ethics approved, registered, prospective, multivariate, placebo-controlled single-blinded, randomised, clinical pilot-trial.

### Ethics Review

The pilot-trial protocol and associated materials have been reviewed and approved by the Macquarie University Human Ethics Committee (Sydney, Australia).

### Settings

Eleven private practices located in Sydney, Australia. The private practices are situated in ten different suburbs around the Sydney region. The distribution of practice locations has been chosen in an attempt to generate a sample that will be reflective of the general population of Sydney.

### Practitioners

Twelve practitioners (five female, seven male) have agreed to donate their time to administer the treatments to the trial participants. The practitioner group consists of nine registered chiropractors, two psychologists, and one psychotherapist. Teachers of NET stipulate that all practitioners must hold a doctorate or master's level degree in the healing arts before they may learn NET. All of the care providers have a minimum of two years experience using NET, and have attained 'NET Certification' status (which denotes the highest level of proficiency recognised within the technique system). These practitioners have been chosen because of their expertise in the NET field. The chief investigator ([name]) will conduct an individual training session for each practitioner involved with the trial. In addition to the training sessions, practitioners will be given a trial reference booklet that details the specifics of the trial. Practitioners will also have phone and email access to the chief investigator at all times in the event that further questions surface following the initial briefing.

### Participants

Participants will respond via a toll-free number to advertisements placed in a variety of different media including; newspapers, magazines, websites, and flyers. An attempt will be made to disseminate hardcopy advertisements in a variety of geographical locations around Sydney. The advertisements will call for participation in a research project examining the influence of a new treatment for hypothyroidism (See Additional File 1). Respondents will be screened over the phone by the chief investigator to determine their eligibility to participate based on a set of inclusion and exclusion criteria. Eligible participants will then be sent a trial information booklet that explains the details of the trial. Participants will be given an opportunity to read through the trial information and make an informed choice as to whether or not they wish to participate in the research. One week after receiving the trial information booklet, potential participants will receive a follow-up telephone call from the chief investigator to ascertain their desire to participate, and to answer any further questions. From this point, willing participants will be sent the salient information to begin their involvement in the trial.

### Informed Consent

In addition to the trial information booklet, all participants will be issued with a copy of the informed consent form. The consent form will detail the names of the individuals involved with the study: chief investigator; supervisors/co-investigators; practitioners. Participants will also be informed that the research is being conducted by the Department of Chiropractic at Macquarie University. A brief description of the study protocols will also provided; duration of the study; outcome measures employed; adverse reactions to treatment and the associated back-up counselling services; ethics approval and contact details of the ethics officer; the right to cease participation at any time; methods for dissemination of results; complaint procedures and privacy policy. Participants will not be asked to alter or cease any existing treatment regimens. Any concurrent treatment regimens will be recorded.

### Sample

The study population will consist of at least 102 individuals with a diagnosis of overt primary hypothyroidism, who are undergoing a variety of management strategies (including no treatment), from Sydney, Australia. A justification for the sample size is provided later.

### Inclusion Criteria

For inclusion, participants will have to meet several criteria: 18 years of age or over; and previous diagnosis of primary overt hypothyroidism by a qualified medical practitioner or specialist. If respondents are being medicated for their thyroid condition, it will be required that they be on a stable dose of medication for at least six months before entering the trial. Any alteration to a participant's medication levels during the trial will be recorded. Respondents who do not meet the inclusion criteria or who meet the exclusion criteria will be excluded from the study.

### Exclusion Criteria

The exclusion criteria will comprise: less than 18 years of age; absent diagnosis of hypothyroidism; iatrogenic hypothyroidism; recent diagnosis of hypothyroidism (within the last six months); presence of co-morbid illness that can impair thyroid hormone production and metabolism; use of medications that can impair thyroid hormone production and metabolism; history of head or neck surgery/radiotherapy; history of significant head trauma; serious co-morbid illness (e.g. cancer); serious co-morbid mental illness (e.g. psychosis); pregnancy or desire to conceive within the study period; physical or mental disabilities that would prevent participants interacting physically and verbally with the care provider during the intervention.

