### Blinding

The allocation of individual participants to treatment groups will be concealed to the chief investigator up until the point of a participant commencing treatment. Individual participants will not be told their group allocation until the completion of their involvement in the trial. All participants allocated to the placebo intervention group will have the opportunity to receive the NET treatment free of charge at the completion of their initial participation. No other incentives will be given for a participant's involvement or follow-up.

Any primary care providers (e.g. endocrinologist) will be blinded to the participant's group allocation. As the practitioners involved in the study will be performing both the NET treatment and the placebo intervention, it will be necessary for the group allocation to be disclosed to these practitioners. Practitioners will be instructed to perform the placebo with the same gusto as the NET treatment. The treating practitioners will have no previous role in the diagnosis or management of the participant's thyroid condition.

Group allocation will be concealed from the pathology company involved in the collection and analysis of the serum outcome measures. Statisticians involved in the analysis of the trial data will be blinded to group allocation.

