### Placebo Protocol

The placebo protocol will align clearly with the NET protocol however the purported therapeutic components of the NET procedure will be removed and replaced with innocuous steps (See Additional File 6.)

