### Primary Outcome Measures

Significant proportions of individuals with 'managed' hypothyroidism continue to experience many of the symptoms associated with the overt, untreated version of the condition [1]. Depression is a common symptom associated with primary overt hypothyroidism [1]. Hypothyroid patients are more likely to experience constitutional and neuropsychiatric complaints as compared to euthyroid individuals [12]. For this reason, the primary outcome will involve the measurement of Depression using of the Depression Anxiety Stress Scale (DASS). The DASS is an instrument for measuring the negative states of depression, anxiety and stress. It is constructed of three self-report scales that enable researchers and clinicians to more concisely define, understand and measure these three clinical states. Each of the three scales contains 14 items that assess different aspects of depression, anxiety and stress [32].

The questionnaire is used to determine negative emotional states versus negative emotional traits. The DASS is based on a dimensional concept of psychological disorder. For this reason, the DASS is not used to allocate patients to specific diagnostic categories. This concept is different to other classificatory systems such as the Diagnostic and Statistical Manual of Mental Disorders (DSM) and International Classification of Diseases (ICD).

All items are rated on a four-point Likert scale from 0 - 3. Scores are determined according to how often particular symptoms were experienced in the past week, with high scores indicating a higher frequency of symptoms. Depression represents a sum of scores from 14 items within the DASS pertaining to depression [32]. States of dysphoria, hopelessness, devaluation of life, self-deprecation, anhedonia, inertia and a lack of interest and involvement are assessed by the 'depression' specific questions within the DASS. Normative data for the Depression scale of the DASS describes a mean of 6.34 with a standard deviation of 6.97. Clinically, depression scores between 0-9 are considered normal. Scores of 10-13 and 14-20 indicate mild and moderate states of depression respectively. Severe and extreme states of depression are defined by scores between 21-27 and 28+ respectively [32].

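### Previous NET treatment is not an exclusion, so people who may recognise the sham can enter a trial whose primary outcome is self-reported

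*Protocol article*

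**What the plan says.** The Exclusion Criteria section is worded as a full list. It opens "The exclusion criteria will comprise: less than 18 years of age; absent diagnosis of hypothyroidism; iatrogenic hypothyroidism" and ends with "physical or mental disabilities that would prevent participants interacting physically and verbally with the care provider during the intervention". Nothing in between concerns earlier NET treatment or being a patient of a trial practitioner. The Inclusion Criteria section requires "18 years of age or over; and previous diagnosis of primary overt hypothyroidism by a qualified medical practitioner or specialist", plus a stable dose for those on medication. The Participants section says that the telephone screen applies these two sets of criteria.

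On blinding, the article states "Individual participants will not be told their group allocation until the completion of their involvement in the trial". The practitioners know the allocation because they deliver both interventions. On existing patients, the one relevant sentence is "The treating practitioners will have no previous role in the diagnosis or management of the participant's thyroid condition".

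On the sham, the Placebo Protocol section says that it follows the NET procedure closely, but that "the purported therapeutic components of the NET procedure will be removed and replaced with innocuous steps". The primary outcome is the DASS depression scale; of the DASS the article says "It is constructed of three self-report scales that enable researchers and clinicians to more concisely define, understand and measure these three clinical states".

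**The concern.** The participant scores the primary outcome, and the practitioner in the room is not blinded. The comparison on depression therefore depends on participants not knowing which intervention they receive. Someone new to NET has nothing to compare the sessions with. Someone treated with NET before does have a reference, over ten sessions. The article describes NET as a distinctive procedure: muscle testing, a named emotion, a recalled memory, a held meridian point and spinal tapping. The Adverse Reactions section foresees uncomfortable recall of past events in the NET group only, so the two arms are not expected to feel identical.

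If some placebo participants recognise the sham and rate their depression as worse for that reason, part of the difference between arms would reflect unblinding and not treatment.

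**Working it through.** **1. Can a NET-experienced person enrol under the text?**

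- Exclusion and inclusion criteria: no item on NET experience.
- Telephone screen: tied to those criteria, so previous NET is not part of it as described.
- Blinding section: the restriction covers the treating practitioner and the thyroid condition. It does not reach NET given by that practitioner for another complaint, or NET given by anyone else.
- Informed Consent section: concurrent treatments are recorded and participants are not asked to stop them. This would capture NET that is still under way, but not NET in the past.
- Statistical Analysis section: the sensitivity analyses address withdrawals, missing data and protocol violations. Previous NET violates nothing in the present criteria, so they do not pick it up.

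The answer is yes. The setting makes it possible in practice: private practices, with practitioners who each have at least two years of NET experience.

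**2. The plan's own sample size, as a base for the illustration.** Inputs from the power section: difference 4, SD 8, one-sided test, 80% power; the 5% level is from the Statistical Analysis section.

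Normal approximation: n = 2 × (1.645 + 0.842)² × 8² / 4² = 49.5, so 50 per group. With the noncentral t distribution, power is 79.9% at 50 and 80.6% at 51 per group. The stated 51 per group is reproduced, and this point does not dispute it.

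**3. Illustrative size of the bias.** Let f be the share of the placebo arm that recognises the sham and b the resulting shift in their score. The documents give neither.

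- Spurious mean difference = f × b.
- Standard error of the difference = 8 × √(2/51) = 1.584.
- False-positive rate with no true effect = probability that a noncentral t with 100 degrees of freedom and noncentrality f × b / 1.584 exceeds the critical value. The two-sided column counts rejections in both directions.

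| f (assumed) | b (assumed) | f × b | One-sided 5% test | Two-sided 5% test |
|---|---|---|---|---|
| 5% | 2 | 0.1 | 5.7% | 5.0% |
| 10% | 2 | 0.2 | 6.4% | 5.2% |
| 10% | 4 | 0.4 | 8.2% | 5.7% |
| 20% | 4 | 0.8 | 12.7% | 7.9% |
| 30% | 4 | 1.2 | 18.6% | 11.7% |

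Both tests are shown because the power analysis is one-sided while the Statistical Analysis section does not name a side. With f = 0 the bias is zero. Because b = 4 equals the whole target effect, a bias of 10% to 20% of the target is simply the assumed f restated; it is not an estimate.

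**The case against.** Several points on the other side carry weight.

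- **Recognition is not certain.** A reader might infer that anyone with NET experience will notice the sham. The article does not support that. The sham is built to follow NET closely, tapping is applied in both arms, and the individual sham steps are in Additional File 6, which is not at hand.
- **The active arm also differs from ordinary NET.** The trial uses a 12-step version and leaves out steps 12 to 14, manual therapy, nutrition and homeopathy. An experienced person could find things missing in either arm, so noticing a difference does not by itself identify the sham. This weakens the mechanism but does not remove it, since the sham also replaces components that the active arm keeps.
- **Few such people may come forward.** Recruitment is by public advertisement for a new treatment, with a toll-free number. Nothing says that participants come from the practitioners' own lists. They are free to respond, but their number may be small or nil.
- **The trial is a pilot** and its analyses are described as exploratory. That lowers the stakes, but the primary comparison is still a placebo comparison and is only as good as its blinding.
- **The text was written late.** The start date is September 2006 and recruitment ends in March 2010, and the article cites a 2009 publication. New exclusions could reach few participants, so the analysis of those already enrolled matters more.

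None of this closes the eligibility gap, which can be read directly from the criteria.

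**Conclusion.** The gap is real: the criteria admit people with previous NET treatment, and the sentence on practitioners' earlier involvement is too narrow to keep them out. The consequence is a possible bias, not a demonstrated one. Its size cannot be derived from the documents. The range of 0.4 to 0.8 points rests entirely on an assumed 10% to 20% recognition in the placebo arm and an assumed 4-point shift, and the true value may be zero.

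Two further readings go too far. One is that no analysis could separate such a bias from a treatment effect. If previous NET is recorded, a comparison without the exposed participants addresses this source, and because exposure precedes randomisation it remains a comparison of randomised groups. The other is that every patient of a trial practitioner must be excluded. A patient who has never had NET has no such reference for recognising the sham, so a different practitioner is enough.

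The point is worth acting on because the remedy is cheap, not because serious harm has been shown.

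**What to change.** - Add previous NET treatment to the exclusion criteria and ask about it at the existing telephone screen.
- Assign any existing patient of a trial practitioner to one of the other practitioners who has not treated them. With twelve practitioners in eleven practices this is possible, though the location may suit some participants less well.
- For participants already enrolled, record NET exposure before trial entry, with the same question in both arms. Word it to refer to the time before entry, because placebo participants are offered NET after they finish. Report the primary comparison at six weeks and six months without the exposed participants as a sensitivity analysis.

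The sample-size calculation does not change. The cost is a small loss of otherwise eligible respondents, one more data item, and a sensitivity analysis that is slightly less precise than the main one if any exposed participants are removed.
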